## Abstract

**Electronic supplementary material:**

The online version of this article (doi:10.1007/s11239-016-1415-7) contains supplementary material, which is available to authorized users.

## Unanswered questions after the acute phase of PE: the need for a large multicenter cohort study

Acute pulmonary embolism (PE) is a frequent cause of death and serious disability [1]. In an epidemiological model derived from six European countries, the estimated number of fatalities related to venous thromboembolism (VTE) amounted to 370,000, or 12 % of all deaths [2]. The risk of an adverse outcome during the acute phase varies widely depending on the clinical severity and the presence of right ventricular dysfunction at presentation [3], with early (30-day) mortality rates ranging from as low as 0.5 % in hemodynamically stable, ‘low-risk’ patients, to over 20 % in those presenting with cardiogenic shock [4]. Moreover, and importantly, the risk to die or develop persistent serious disability extends far beyond the acute phase of PE [5]. In earlier follow-up studies, as many as 25 % of the patients did not survive the first year after diagnosis, with the majority of deaths being related to underlying conditions such as cancer or chronic heart disease [6–8]. Consistently with these data, a cohort study of 866 patients who were retrospectively identified as having suffered acute PE (unprovoked in 308 patients; provoked in 558 patients), reported that 30 % of the study population died over a median follow-up period of 3.3 years [9]. Of 259 recorded deaths in that study, 110 were due to malignancy, 67 to recurrent PE, 30 to other cardiovascular disease, and the remaining 52 to other causes; in comparison, only 8.7 % of patients without PE died during the same study period [9]. Of note, there are no recent large multicenter cohort studies to provide contemporary, prospective data on long-term survival rates after PE.

Understanding and, as the following step, predicting the clinical course of a patient after acute PE is a far more complex task than answering the ‘dead or alive’ question. The available data from the follow-up of retrospectively identified patients, or from prospective studies of relatively small single-center cohorts (reviewed in [10]), suggest that more than 50 % of patients continue to complain of dyspnea and/or poor physical performance 6 months to 3 years after the index event, and up to 75 % perceive their own health status as being worse than before the acute PE episode. If confirmed in adequately powered follow-up studies, these numbers could be translated into a substantial clinical impact and socio-economic burden imposed by PE over the long term, far beyond that already acknowledged for the acute phase of the disease [11, 12]. At the far end of the severity spectrum of ‘late PE sequelae’ is a life-threatening disease termed chronic thromboembolic pulmonary hypertension (CTEPH). This progressive vasculopathy is thought to result from incomplete resolution of single or recurrent pulmonary emboli arising from sites of venous thrombosis [1, 13]. Although the diagnosis and management of CTEPH have made progress in recent years [14, 15], its true incidence and temporal pattern of development following an episode of acute PE remain obscure. The large margin of error in reported incidence rates of CTEPH (between 0.1 and 9.1 % within the first 2 years after a symptomatic PE event), is most likely due to referral bias, absence of early symptoms, and the difficulty in differentiating acute PE from an episode superimposed on pre-existing CTEPH [13, 16]. Moreover, and importantly, its ‘prodromi’, i.e. the clinical, functional and hemodynamic changes corresponding to early, possibly reversible stages of developing CTEPH, have not been systematically investigated.

The ongoing follow-up after acute pulmonary embolism (FOCUS) study will prospectively enroll and systematically follow, over a 2-year period and with a standardized comprehensive program of clinical, echocardiographic, functional and laboratory testing, a large multicenter prospective cohort of unselected patients (all-comers) hospitalized for acute symptomatic PE. FOCUS has been designed to possess adequate power which will enable it to provide answers to the above relevant remaining questions regarding the patients’ long-term morbidity and mortality after PE. It should thus be able to provide evidence for future guideline recommendations on which patients should be selected for long-term follow-up after PE, and possibly for ‘CTEPH screening’, and which modalities this follow-up should include.

## Study population and objectives of FOCUS

A total of 1000 consecutive patients with acute symptomatic, objectively diagnosed PE will be prospectively included in FOCUS on the basis of the eligibility criteria listed in Table 1. FOCUS explicitly aims to enroll ‘all-comers’ with PE, irrespective of the clinical severity, evidence of right ventricular dysfunction, or size or extent of pulmonary emboli. The primary objective is to determine the cumulative incidence of, (1) CTEPH, and (2) persisting or progressive functional and/or hemodynamic post-PE impairment (PPEI) over a 2-year follow-up period after an index episode of acute symptomatic PE. Secondary objectives are to assess, among others, overall and disease-specific long-term mortality, the incidence of major adverse cardiovascular events (such as acute myocardial infarction, stroke, or VTE recurrence), predictors as well as indicators of functional/hemodynamic impairment, fatal bleeding complications associated with long-term anticoagulant treatment for VTE, and the patients’ generic and disease-specific quality of life.

**Table 1 Tab1:** Eligibility criteria

Inclusion criteria	Exclusion criteria
Objectively confirmed diagnosis of acute symptomatic PE by CTPA, V/Q lung scan, or invasive selective pulmonary angiography, according to established diagnostic criteria, with or without symptomatic DVT	Patients in whom the diagnosis of PE is an asymptomatic incidental finding during diagnostic work-up for another disease
Age ≥18 years	Patients with previously diagnosed CTEPH
Written informed consent obtained before enrollment	Previous enrollment in this study

*CTEPH* chronic thromboembolic pulmonary hypertension, *CTPA* computed tomographic pulmonary angiography, *DVT* deep vein thrombosis, *PE* pulmonary embolism, *V*/*Q* ventilation-perfusion

## Patient outcomes

The complete list of primary, secondary, and safety outcomes of FOCUS is provided in Table 2. Confirmed diagnosis of CTEPH during the 2-year follow-up period is the first primary outcome. However, as the occurrence of CTEPH is expected to be low and the absolute number of events small, even with this large patient population, PPEI has been defined as a co-primary outcome. This approach, which is explained in the statistical analysis section below, has its rationale in the assumption that persisting or progressive functional and/or hemodynamic impairment after acute PE is an early indicator of, and in statistical terms a ‘necessary condition’ for, the subsequent development of CTEPH. PPEI was defined by the FOCUS steering committee based on (and extrapolated from), (1) previously proposed prognostic criteria for pulmonary hypertension [17], (2) practical guides to cardiopulmonary exercise testing for evaluation of pulmonary hypertension and chronic thromboembolic disease [18, 19], and (3) the risk assessment of pulmonary (arterial) hypertension at follow-up visits as recommended in the 2009 [20] and recently updated [14] guidelines of the European Society of Cardiology and the European Respiratory Society. A detailed overview of the assessment and classification of individual indicators of PPEI ((a) and (b) parameters) is provided in Table 3.

All outcomes will be adjudicated by an independent Clinical Events Committee (CEC).

**Table 2 Tab2:** Primary, secondary, and safety outcomes

Co-primary outcomes^a^	
(1) Confirmed diagnosis of CTEPH at any time during the 2-year follow-up	
(2) Post-PE impairment, defined by deterioration (compared to the findings at discharge, or to the previous follow-up visit) by at least one category, or persistence of the greatest severity category, in ≥1 of ‘a’ parameters plus deterioration by at least one category, or persistence of the greatest severity category, in ≥1 of ‘b’ parameters	
(a) Echocardiographic parameters of pulmonary hypertension and/or RV dysfunction^b^	(b) Clinical, functional and laboratory parameters of RV failure^b^
(a1) RV basal diameter (D1)	(b1) New appearance of symptoms or progression of existing symptoms
(a2) RA end-systolic area	(b2) Clinical evidence of RV failure
(a3) TAPSE	(b3) Syncope
(a4) LV eccentricity index	(b4) WHO functional class
(a5) Estimated RA pressure	(b5) Six-minute walking distance
(a6) Systolic TR jet velocity	(b6) BNP or NT-proBNP plasma levels
(a7) Pericardial effusion	(b7) Cardiopulmonary exercise testing

Secondary outcomes	
(1) Overall and disease-specific mortality during follow-up	
(2) Symptomatic recurrence of DVT or PE	
(3) Rehospitalization for reasons related to VTE, CTEPH, or complications of their treatment	
(4) New diagnosis of cancer	
(5) Acute myocardial infarction	
(6) Stroke	
(7) Functional limitation (peak O_2_ consumption and systolic blood pressure on cardiorespiratory exercise testing; six-minute walking distance and Borg dyspnea index)	
(8) Evidence of pulmonary hypertension/right ventricular dysfunction on echocardiography	
(9) Evidence of pulmonary vascular abnormalities on cardiopulmonary exercise testing^c^	
(10) Generic and disease-specific quality of life using the EQ-5D and the PEmb-QoL questionnaires	

Safety outcomes	
(1) Major bleeding during hospitalization for the index event, based on the ISTH definition [21]	
(2) Fatal bleeding at any time during follow-up	

*BNP* brain natriuretic peptide, *CTEPH* chronic thromboembolic pulmonary hypertension, *EQ-5D* Euro Quality of life five dimensions (questionnaire), *ISTH* International Society on Thrombosis and Haemostasis, *NT-proBNP* N-terminal pro-brain natriuretic peptide, *PE* pulmonary embolism, *PEmb-QoL* Pulmonary Embolism Quality of Life (questionnaire), *RA* right atrial, *RV* right ventricular, *TAPSE* tricuspid annular plane systolic excursion, *TR* tricuspid regurgitation, *VTE* venous thromboembolism, *WHO* World Health Organization

^a^See statistical analysis for details

^b^See Table 3 for severity classification of individual findings and parameters

^c^Indicated by at least one of the following: PETCO_2_ at AT (end-tidal partial carbon dioxide pressure at anaerobic threshold) <31.33 mmHg; P(a-ET)CO_2_ >5.18 mmHg; EQ O_2_ (oxygen ventilatory equivalent) >30.5; EQ CO_2_ (carbon dioxide ventilatory equivalent) >35.5; VE/VCO_2_ slope (ventilator efficiency for carbon dioxide) >37.5; P(A-a) O_2_ (alveolar–arterial oxygen gradient) >36.97 mm [22]

**Table 3 Tab3:** FOCUS classification of the severity of post-PE abnormalities

Determinants of post-PE impairment	Normal or mild/low			Moderate			Severe/high	
(a) Echocardiographic parameters								
RV basal diameter (D1)	≤4.2 cm				>4.2 cm			
RA end-systolic area	≤18 cm^2^				>18 cm²			
TAPSE	≥1.6 cm				<1.6 cm			
Eccentricity index of LV	≤1.0				>1.0			
Estimated RA pressure	*0–5 mmHg* IVC diameter ≤2.1 cm and inspiratory collapse >50 %			*10 mmHg* IVC diameter ≤2.1 cm and collapse <50 %; or IVC diameter >2.1 cm and collapse >50 %			*15 mmHg* IVC diameter >2.1 cm and collapse <50 %	
Systolic TR jet velocity	<2.8 m/s			2.9–3.4 m/s			>3.4 m/s	
Pericardial effusion	No				Yes			
(b) Clinical, functional and laboratory parameters								
New appearance of symptoms or progression of existing symptoms	No				Yes			
Clinical evidence of RV failure	No				Yes			
Syncope	No				Yes			
WHO functional class	I or II				III or IV			
Six-minute walking distance	>500 m			300–500 m			<300 m	
BNP or NT-proBNP plasma levels	BNP <50 ng/L			BNP 50–300 ng/L			BNP >300 ng/L	
	NT-proBNP <300 ng/L			NT-proBNP 300–1400 ng/L			NT-proBNP >1400 ng/L	
Cardiopulmonary exercise testing (peak O_2_ uptake and systolic BP)^a^	>64.5 % and >120 mmHg	>64.5 % and ≤120 mmHg	46.3–64.5 % and >120 mmHg	46.3–64.5 % and ≤120 mmHg	34.1–46.3 % and >120 mmHg	34.1–46.3 % and ≤120 mmHg	<34.1 % and >120 mmHg	<34.1 % and ≤120 mmHg

*BNP* brain natriuretic peptide, *BP* blood pressure, *IVC* inferior vena cava, *LV* left ventricle, *NT-proBNP* N-terminal pro-brain natriuretic peptide, *RA* right atrial, *RV* right ventricular, *TAPSE* tricuspid annular plane systolic excursion, *TR* tricuspid regurgitation, *WHO* World Health Organization

^a^Peak O_2_ uptake as percentage of predefined value; systolic blood pressure measured at peak exercise

## Study design and flow

FOCUS is a prospective, multicenter, observational cohort study. The study protocol does not dictate any diagnostic or therapeutic interventions. On the other hand, the participating sites, which are high-volume centers with a long-standing experience in PE and pulmonary hypertension management, have harmonized their existing follow-up protocols and agreed that they will adhere to the follow-up schedule and workup presented in Table 4, which they consider as ‘best medical care’.

Detailed demographic and clinical data, diagnostic and therapeutic procedures, and outcome variables are recorded in an electronic case report form (eCRF). Regular follow-up visits are performed on discharge, and at 3, 12, and 24 months, as part of the best medical care standard at the participating centers.

**Table 4 Tab4:** Data collection schedule

Variable	In-hospital		Follow-up		
	Enrollment	Discharge	3 months	12 months	24 months
Medical history	x				
Demographic data^a^	x				
Clinical examination^b^	x		x	x	x
Imaging (PE diagnosis)	x				
Echocardiography	x	x	x	x	x
Cardiopulmonary exercise testing			x	x	x
Laboratory diagnostic and safety tests^c^	x	x	x	x	x
Pharmacological treatment	x	x	x	x	x
Hemodynamic collapse	x	x	x	x	x
Survival status		x	x	x	x
Rehospitalization			x	x	x
Stroke		x	x	x	x
Symptomatic recurrent DVT/PE		x	x	x	x
Bleeding events		x	x	x	x
Functional status^d^			x	x	x
Diagnostic work-up for CTEPH^e^			x	x	x
Generic quality of life^f^			x	x	x
Disease-specific quality of life^g^			x	x	x

*CTEPH* chronic thromboembolic pulmonary hypertension, *DVT* deep vein thrombosis, *PE* pulmonary embolism

^a^Date of birth, gender, height, weight

^b^Presentation and symptomatology, vital signs; 12-lead ECG

^c^Serum creatinine, creatinine clearance [MDRD-estimate], TSH, O_2_-saturation [pulse oximetry], hematocrit, thrombocytes, leucocytes, aPTT, PT, INR, troponin T or I, NT-pro-BNP, BNP, CRP, d-dimer

^d^WHO functional class, Borg dyspnea index

^e^CT pulmonary angiography, V/Q scan; selective pulmonary angiography, right heart catheterization

^f^EQ-5D questionnaire [23]

^g^PEmb-QoL questionnaire [24]

## Biobanking substudy: the FOCUS BioSeq project

A multicenter biobanking substudy ‘Biochemical and Genetic Biomarkers in Sequelae of Acute Pulmonary Embolism Study (FOCUS BioSeq)’ is being conducted within the FOCUS cohort. Currently, a number of biomarkers have a place in PE management; most of them, including d-dimers, cardiac troponins, and natriuretic peptides, are used in the differential diagnosis or risk stratification of acute PE [1]. On the other hand, a systematic biochemical and genetic characterization of PE survivors over the long term is missing in the literature. Thus, the primary objective of the FOCUS BioSeq substudy is to identify and evaluate molecular and genetic markers for late sequelae of acute PE. Further objectives are to evaluate novel and established biomarkers for cost effectiveness and suitability in long-term management strategies, and as predictors of the response to pharmacotherapy.

To achieve these goals, a decentralized and pseudonymized sample collection with centrifugal (standardized) preprocessing of plasma, serum and urine with short-term storage at −80 °C is being implemented in the participating study centers. For sample shipment to the central biobanking facility, pseudonyms and temperature control are maintained. On arrival, single sample aliquots are indexed for retrieval. Nucleic acids (DNA and RNA) are centrally isolated and quantity- and quality-controlled. Shipped, indexed and quality-controlled biomaterials are subsequently long-term stored in a centralized, 2-D barcoded and mirrored biobank at −80 °C. The following biomaterial specimens are collected in sufficient volumes for biomarker characterization and progression analysis in baseline and follow-up investigations: EDTA plasma, citrated plasma (3.2 %), serum, whole blood DNA and whole blood RNA (see Supplementary Table 1). Samples are collected and processed according to standard operating procedures (SOP). The FOCUS BioSeq biobanking procedures are illustrated in Fig. 1. Collection of biomaterial and optionally genetic examinations or exchange of biomaterial and data with collaboration partners are carried out after informed written consent has been provided by the study participant.

**Fig. 1 Fig1:**
[figure not shown]
Biobanking workflow in the FOCUS BioSeq substudy

From the processed specimens, various biomarkers will be determined; a special focus will be put on biomarkers with known or expected relevance for the (pathophysiology of) circulation, hemostasis, inflammation, immunity, and kidney disease. High-throughput screening approaches will spotlight new potential biomarkers for sequelae of PE: Collected and purified DNA will be used for array-based genome-wide investigations aiming at discovering new genetic loci (further investigated by sequencing methods) which may predict the future clinical course of the disease or the response to drugs. Extracted RNA specimen like cellular mRNA, small non coding RNA or miRNA can be used for sequence probe based differential gene expression investigations. Epigenetic modifications on DNA samples or newly identified and known protein biomarkers at defined time points or in serial measurements from the follow-up assessment might be of prognostic relevance.

## Sample size calculation and statistical analysis

For sample size calculation, we assumed that the annual incidence rate of CTEPH in unselected patients who have suffered an episode of acute symptomatic PE (either provoked or unprovoked) is at least five times higher than the very low rate of 0.16 per 100 patients per year reported in one of the largest cohorts published to date [25], i.e. 0.8 per 100 patients per year. We further assumed that overall death rates and case-mix (high risk versus intermediate-risk versus low risk PE) will be similar to that previous study [25], and that there will be a ≤5 % loss-to-follow-up per year in addition to the administrative censoring and deaths. Following these assumptions, the cumulative incidence of CTEPH at 2 years is expected to amount to 1.3 %. In this case, our simulations indicate that a study population of 1000 patients will provide roughly 90 % power to reject the H_0_ hypothesis that the cumulative incidence of CTEPH at 2-year follow-up is 0.27 % (the cumulative incidence corresponding to the rate reported in [25]).

For a subgroup with an expected size of about 500 patients with unprovoked PE, i.e. an index PE event in the absence of reversible predisposing factors, an exploratory analysis will be performed. In this analysis, a power of more than 80 % can still be achieved to reject the H_0_ hypothesis that the cumulative incidence of CTEPH at 2-year follow-up is 0.27 %, if the hazard in the subgroup is at least six times higher than that previously reported for the unselected PE population [9, 25].

All enrolled patients will be included in the statistical analysis. Hierarchical testing will be used for the two co-primary outcomes, CTEPH and PPEI, assuming that all patients will present with PPEI before or at the time of the diagnosis of CTEPH. Therefore, we will first test whether the cumulative incidence of PPEI is significantly higher than 0.27 % at 2 years, and, if this is the case, whether the cumulative incidence for CTEPH also differs from the same threshold. The overall level of significance will be set to α = 0.05. Both tests will have a local power of approximately 90 %. Testing will be performed by checking whether the 95 % confidence interval of the 2-year Aalen-Johansen estimate of the cumulative incidence function (CIF) contains the value 0.27 %.

For the analysis of the primary outcome, it is assumed that CTEPH and PPEI can be considered independent of possible deaths during follow-up (e.g., mortality associated with cancer, myocardial infarction or stroke); if the cause of death is not independent from PPEI, the analysis for the primary outcome assumes that CTEPH or PPEI is always diagnosed before death. While these assumptions can reasonably be expected to hold true for PPEI, they might be less robust for CTEPH. Therefore, this latter point will be addressed by sensitivity analyses. The planned secondary and sensitivity analyses are listed in the Supplementary Material.

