## Innovative features and expected impact of FOCUS

Existing data suggest that incomplete thrombus resolution as well as persisting hemodynamic abnormalities and functional limitation over the long term occur quite frequently after acute PE. For example, between 30 and 52 % of the patients who survive the acute phase have been reported to have evidence of residual perfusion defects for at least 1 year after the acute event [26–29]; furthermore, the proportion of patients with some degree of persistent pulmonary hypertension after acute PE ranged between 40 and 69 % [30, 31]. However, these data are to be interpreted with caution, since the single-center cohort studies conducted thus far included rather small numbers of patients, the echocardiographic parameters used to assess the hemodynamic status post PE did not rigorously follow the standards proposed by scientific societies [32], and a correlation of ultrasound or thrombus imaging findings with the severity of the patients’ residual symptoms or the degree of functional limitation at follow-up could not be established [33]. These limitations unavoidably generate a high degree of uncertainty in estimating and predicting late outcomes after PE, more specifically the risk of developing CTEPH [5] as well as the entirety of persisting or progressive abnormalities belonging to the so-called ‘post-PE syndrome’ [10]. In this context, it also needs to be mentioned that some patients who have had PE may present with chronic symptomatic disease, which is morphologically indistinguishable from CTEPH but associated with normal pulmonary hemodynamics at rest (on echocardiography and right heart catheterization). Although these patients are also considered to have CTEPH and are managed accordingly, the pathophysiology of this ‘chronic thromboembolic pulmonary vascular disease’ remains obscure, and an exact definition and appropriate terminology is still lacking. In view of all these uncertainties, even the most recent guidelines are unable to provide clear recommendations on who, how often, and with what modalities should be followed after acute PE [1, 14].

In order to effectively address these clinically relevant issues, the FOCUS study is equipped, by its design, with the following innovative elements:

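### PPEI is tested against a CTEPH benchmark of 0.27 %, so the first hierarchical test is close to a formality, and the stated 90 % power is only its floor

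*Protocol article*

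**What the plan says.** All of the following is in the section on sample size calculation and statistical analysis, unless noted.

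- The null value is a 2-year cumulative incidence of 0.27 %, described as "the cumulative incidence corresponding to the rate reported in" an earlier cohort. That rate is for CTEPH (0.16 per 100 patients per year).
- Under the alternative, CTEPH reaches 1.3 % at 2 years, and "our simulations indicate that a study population of 1000 patients will provide roughly" 90 % power.
- The co-primary outcomes are tested hierarchically, PPEI first: "Therefore, we will first test whether the cumulative incidence of PPEI is significantly higher than" 0.27 %. If that succeeds, the second test asks "whether the cumulative incidence for CTEPH also differs from the same threshold".
- The order rests on the assumption that every patient with CTEPH has PPEI by the time CTEPH is diagnosed.
- "The overall level of significance will be set to" 0.05. The decision rule is whether the 95 % "confidence interval of the 2-year Aalen-Johansen estimate of the cumulative incidence function (CIF) contains the value" 0.27 %.
- "Both tests will have a local power of approximately" 90 %.

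The section on patient outcomes explains that PPEI was made co-primary because few CTEPH events are expected. Table 2 defines PPEI as worsening by a category, or remaining in the worst category, in at least one of seven echocardiographic parameters and also in at least one of seven clinical, functional or laboratory parameters. No expected PPEI incidence and no PPEI-specific null value is given.

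**The concern.** A null value should be a figure that the outcome could plausibly fail to exceed. The value 0.27 % describes how often a rare disease was diagnosed in one earlier cohort. PPEI is a broader state that was added because it should be more common. Exceeding a CTEPH figure says little about PPEI.

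Two statements are affected. First, the hierarchy suggests that CTEPH is tested only after a real hurdle has been cleared. With one shared threshold and CTEPH nested within PPEI, there is no such hurdle. Second, a power of about 90 % for PPEI implies an expected PPEI incidence of about 1.3 %, which would mean that hardly any patient has PPEI without CTEPH. That conflicts with the reason for adding PPEI.

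At stake is how one of two co-primary results is read. A report that PPEI is significantly above 0.27 % could be taken as evidence when it was almost settled in advance. The quantity that matters, the PPEI incidence itself, has no stated precision target.

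**Working it through.** **Inputs from the article.** N = 1000; null 0.27 % for both tests; CTEPH alternative 1.3 %; two-sided 95 % confidence interval; loss to follow-up of at most 5 % per year; stated power about 90 % for both tests.

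**Inputs assumed.** PPEI incidence, which the article does not give, is varied from 1.3 % (the floor set by nesting) to 50 %. The death hazard in the simulations is 0.10 to 0.20 per year.

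**Step 1: rejection count.** With a plain (Wald) interval, the test rejects upward when p − 1.96 × √(p(1 − p)/1000) exceeds 0.27 %.
- 8 events: 0.80 % − 1.96 × 0.282 % = 0.25 %, no rejection.
- 9 events: 0.90 % − 1.96 × 0.299 % = 0.31 %, rejection.

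Nine events in 1000 are enough. Exact or log-log intervals need only seven, so nine is the least favourable case.

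**Step 2: reproduce the plan's figure for CTEPH.** P(X ≥ 9) for a binomial with n = 1000 and p = 1.3 % is 90.2 %. A simulated Aalen-Johansen analysis with plain intervals, CTEPH hazard 0.008 per year, 5 % annual loss and the assumed death hazards gives 88 to 92 %. With the exact interval the power is 97.5 %. The stated 90 % therefore reproduces for CTEPH.

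**Step 3: the same test applied to PPEI.** Power is P(X ≥ 9) with n = 1000.

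| True 2-year PPEI incidence | Power against 0.27 % |
|---|---|
| 1.3 % | 90.2 % |
| 1.5 % | 96.4 % |
| 2.0 % | 99.8 % |
| 2.5 % | 99.99 % |
| 3.0 % | above 99.999 % |
| 5 % to 50 % | 100 % to the digits computed |

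Simulated Aalen-Johansen analyses with deaths and losses give 99.6 % at 2.0 % and 100 % at 3.3 %, 8 % and 15 %. If only 500 patients could be evaluated and nine events were still required, power at 5 % would be 99.99 %.

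**Step 4: the hierarchy.** If every CTEPH case is also a PPEI case, nine or more CTEPH events imply nine or more PPEI events. Whenever CTEPH is found to exceed 0.27 %, PPEI has already been found to exceed it. The first step removes no rejection of that kind.

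**Step 5: precision of the PPEI estimate.** The half-width is 1.96 × √(p(1 − p)/n).
- n = 1000, p = 10 %: 1.96 × 0.949 = 1.9 percentage points.
- n = 1000, p = 20 %: 1.96 × 1.265 = 2.5 percentage points.
- As a rough allowance for losses, n = 1000 × 0.95² ≈ 902 gives 1.96 × 0.999 = 2.0 and 1.96 × 1.332 = 2.6 percentage points.

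**The case against.** The strongest reply is that nothing important is damaged, and much of it stands.

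- **The estimate is already planned.** The test is read from the confidence interval of the 2-year Aalen-Johansen estimate, so the PPEI incidence and its interval will be produced and will serve the primary objective. A reader might infer that this co-primary outcome carries no information. The documents do not support that; only the comparison with 0.27 % is empty.
- **The power statement errs on the safe side.** A reader might infer that the study is underpowered for PPEI. The opposite holds: under nesting, 90 % is a lower bound. The sample size was derived from CTEPH and does not change.
- **Alpha is sound.** In a fixed sequence CTEPH is tested at the full 0.05, with or without the PPEI step.
- **Certainty is not documented.** A reader might treat the cited frequencies as PPEI rates, for example "the proportion of patients with some degree of persistent pulmonary hypertension after acute PE ranged between 40 and" 69 %, or the complaints of dyspnea or poor performance in more than half of patients. They are not PPEI rates. PPEI requires an echocardiographic and a clinical, functional or laboratory criterion together. The article itself urges caution about the hemodynamic data and notes that imaging findings had not been shown to correlate with symptoms.
- **Measurement noise proves nothing here.** A reader might also infer that chance category changes across 14 parameters alone would exceed 0.27 %. The article gives no error rates for them, and an independent committee adjudicates all outcomes.

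What the reply does not answer is that the article itself sets a CTEPH benchmark as the PPEI null and assigns the CTEPH power to the PPEI test. Nesting explains the order of testing. It does not make the threshold meaningful for PPEI.

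**Conclusion.** The point holds in a limited form. The PPEI null belongs to a different outcome, the first step cannot block a finding that CTEPH exceeds 0.27 %, and 90 % is a floor for PPEI power rather than its expected value.

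The size depends on an incidence that the article does not state. At 1.3 % the power is about 90 %. From about 2 % upward it is at least 99.6 %, and the test result tells the reader almost nothing. An incidence of 2 % or more is an assumption, although it fits the stated reason for adding PPEI. The argument also relies on the plan's own assumption that every CTEPH patient has PPEI first.

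The CTEPH test, its power, the overall alpha, the sample size and the PPEI estimate are all unharmed. This should be corrected because a co-primary claim and its power are described inaccurately, but it does not threaten the validity of the study.

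**What to change.** Preferred change:

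1. Drop the comparison of PPEI with 0.27 %. Make the 2-year Aalen-Johansen cumulative incidence of PPEI with its 95 % confidence interval the co-primary result.
2. State the expected precision: a half-width of about 1.9 percentage points at an incidence of 10 % and 2.5 at 20 % with 1000 fully observed patients, slightly wider with the losses allowed for.
3. Test CTEPH against 0.27 % at alpha 0.05, as now in effect, and limit the statement of about 90 % power to CTEPH.

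Alternative: keep a PPEI test, but give a null value justified for PPEI, an expected PPEI incidence and the matching power.

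The preferred change affects wording only. It needs no extra patients, visits or data, and gives up only a significance statement of little value. The alternative also requires an external basis for the PPEI null and expected incidence, which the article does not contain.
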